#### Control group (CG)

Participants assigned to this group will be strongly encouraged to keep their usual life-style, or continue their usual physical activity, generally of low intensity, consisting in long walks, and/or stretching, toning and/or balance exercises, or posture education. Control subjects changing the PA intensity from light (RPE < 11) to moderate or vigorous (RPE > 12) are excluded from the group.

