**Methods/design:**

EPD is a parallel group, double-blind, randomized controlled trial. Community-dwelling volunteers aged 50 years or more are being recruited from different community centers and screened for eligibility. Enrolled subjects are being divided in 3 groups: a) without subjective or objective cognitive impairment, b) with subjective memory complaints, and c) with mild cognitive impairments. Participants in each group (at least 180) are being randomly assigned (1:1) to an experimental group, performing a supervised training including aerobic and resistance exercises of moderate/high intensity, or to a control group. Primary outcome will be 48-months changes in Mini Mental State Examinations. Secondary outcomes will be changes in several cognitive tests including a composite cognitive score. Time points will be at baseline, and at 6, 12, 24, 36 and 48 months. Statistical analysis will be done as intention to treat, complete case and mixed model analysis.

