### Procedures

After the baseline assessments, the subjects in each category group (A, B and C) is identified by a progressive number and randomly assigned in a ratio of 1:1 to experimental or control group, using a list of random numbers generated by a statistical software (SPSS). The list was kept in a sealed envelope and a researcher, not directly involved in the recruitment and in the evaluation of the participants, assigned the allocation numbers.

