#### Experimental group (EG)

Participants randomized to the experimental group are asked to participate in one-hour exercise classes, three times a week, for 48 months. The classes, with a maximum of 12 participants, are organized in the rooms of the University Sports Center of the University of Molise and are led by experienced instructors trained to supply the same program in each class. Exercise program is individualized based on physical function, physical fitness level, health status, and exercise responses.

Exercise intensity are measured according to the Borg’s Rating of Perceived Exertion (RPE), a 6-to-20 points scale [36] on which a score < 11 is considered an effort equal to a light exercise, 12–13 to a moderate exercise, and 14–17 to a vigorous exercise [37]. The RPE scales were extensively used and demonstrate moderate to strong validity compared with other measures of cardiorespiratory exercise intensity, such as percent of the maximal oxygen uptake (% VO_2max_), percent of the maximum heart rate (% HRmax), and blood lactate concentrations [37]. The training program and RPE system were chosen and designed to be easily reproducible at home, to promote a physical active life-style also after the end of the study.

The exercise programs offer a wide variety of exercises including aerobic, strengthening/endurance (resistance), and flexibility (stretching) exercises. Each session consists of a warm-up, aerobic, resistance, cool-down and stretching phase.

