The *warm up phase* lasts 5–10 min and consists of light-to-moderate intensity (RPE 10–12) aerobic activity. During this phase, fitness ergometers, such as treadmill and/or stationary bicycle, or walking/jogging activities are used to activate the biggest muscular groups. Then, the *aerobic phase* lasting 15–20 min is performed by treadmill, stationary bike, arm-cycle ergometer and/or running. Duration and intensity of exercise are gradual over time, starting with multiple bouts (< 2 min) of light to moderate intensity (RPE max 12–13) exercises up to two 10-min bouts of moderate to vigorous exercise (RPE max 16–17), after several week of training. Subsequently, the *resistance phase,* lasting 20–25 min and involving the principal muscular groups of limbs and trunk, is carried out by bodyweight exercises (calisthenics) and dumbbells up to 2 kg. Duration and intensity are also progressive over time, starting with 2 series of 10 repetitions (RPE max 11–12) up to 6 series of 20 fast repetitions (RPE max 14–16), for each muscular group. Finally, the *stretching phase*, lasting less than 10 min, consists in flexibility exercises for each major muscle/tendon groups. Participants are invited to stretch to the point of feeling tightness or slight discomfort, hold a static stretch for 20–30 s and repeat the exercise 2–3 times for each muscle/tendon group.

The instructors monitor exercise intensity during all sessions taking care of the needs of the participants.

Participants with a number of absences > 50% are considered not adherent to the training.

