### Outcomes

The primary outcome of the study will be 48-month change in MMSE scores. Secondary outcome will be 48-month change in neuropsychological test scores, including FAB, RAVLT, PMT, Stroop Color Word Interference Test, Attentive Matrices, Raven’s Progressive Matrices, TMT, Copying of Drawings with and without landmarks, and in GDS, SF-36, MAC-Q, PASE and AAHPERD fitness scores. Another outcome measure will be a composite cognitive score, which will be calculated for assessing the overall changes in cognitive performance. Each cognitive score will be standardized into a z score, by subtracting the baseline mean and dividing by the baseline standard deviation of the group. Regarding tests with more than 1 part, the standardization will be performed for each individual part. All z scores will be then averaged to calculate the composite cognitive score at each of the five time points (baseline, and 12, 24, 36 and 48 months). A positive score will point out a gain in cognitive performance, while a negative score a loss.

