### Randomization

After the baseline assessment, the participants of each category groups A, B and C were randomly assigned to one of the two groups (CG and EG) by using 1:1 blind randomization. For the randomization, a scheme generated via a computerized random number generator was used.

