### Statistical analysis

Data will be analysed using the SPSS statistical software package (IBM, v.20.0, Chicago, IL, USA). Variables will be examined for outliers and extreme values by means of box and normal quantile-quantile plots, Shapiro-Wilk’s and Kolmogorov-Smirnov’s tests. When normal distribution cannot be accepted, the transformed variable (square, square root, logarithmic, reciprocal of square root or reciprocal transformations) will be reviewed. For normally distributed continuous variables, arithmetic means and SDs will be calculated, while for not normally distributed continuous variables, median, 25th and 75th percentiles will be calculated, according to the shaped distributions of two groups, as assessed by visual inspection of population pyramids. Sampling homogeneity (or baseline differences between groups) will be examined by means of chi-square (χ^2^) for categorical variables, independent-samples t-test for normally distributed variables and Mann-Whitney U test for not normally distributed variables. Differences between groups (experimental group vs. control group) and changes in the cognitive performance during the trial will be evaluated by means of Repeated Measures Analysis of Covariance (RM-ANCOVA) in the intention to-treat and complete-case analyzes, or with Linear Mixed Model analysis (LMM). The evaluations in the different time-points will be considered as the within-subjects factor whereas the two groups will be considered as between factor. Age, education level and gender will be included as covariates. The assumptions of equality of variances and sphericity will be assessed by means of Levene’s test and Mauchly’s test, respectively. The Greenhouse-Geisser or the Huynh-Feldt correction will be applied if the assumption of sphericity will be violated. Post-hoc independent-samples t-test will be performed to detect significant differences among trial conditions.

A *p*-value < 0.05 will be considered statistically significant.

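### Randomised controls who become more active are excluded, with no matching exclusion stated for the experimental arm; on its plain reading this conflicts with intention to treat and can bias the 48-month comparison

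*Protocol article*

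**What the plan says.** Randomisation comes first. The Randomization section states: "After the baseline assessment, the participants of each category groups A, B and C were randomly assigned to one of the two groups". The Procedures section gives the ratio as 1:1 within each category group.

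Two rules then deal with departures from the assigned condition:

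- Control group (CG): "Control subjects changing the PA intensity from light (RPE < 11) to moderate or vigorous (RPE > 12) are excluded from the group".
- Experimental group (EG): "Participants with a number of absences > 50% are considered not adherent to the training". The article attaches no consequence to this label.

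On the analysis, the abstract says: "Statistical analysis will be done as intention to treat, complete case and mixed model analysis". The Statistical analysis section has: "RM-ANCOVA) in the intention to-treat and complete-case analyzes, or with Linear Mixed Model analysis (LMM". Under Outcomes: "The primary outcome of the study will be 48-month change in MMSE scores".

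The article does not say whether an excluded control continues to attend assessments, or whether the data of that control enter any of these analyses.

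**The concern.** An intention-to-treat comparison keeps everyone in the arm to which chance assigned them. The control rule removes people for something they do later, and what they do (taking up moderate or vigorous activity) is close to the exposure under test. The controls who remain are then a selected group, while no corresponding exclusion is stated for the experimental arm. Baseline balance from randomisation no longer protects the comparison.

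The planned analyses do not clearly repair this. A complete-case analysis loses these people if their follow-up ends. A mixed model can use their earlier visits only if those data are kept, and it then relies on data being missing at random given what is in the model. The listed covariates are age, education level and gender, with no measure of activity.

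At stake is the contrast in the primary outcome within each of the three category groups. Follow-up lasts 48 months, which leaves ample time for controls to change their habits.

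A smaller inconsistency sits in the trigger. The Experimental group section classes RPE "12–13 to a moderate exercise, and 14–17 to a vigorous exercise", whereas the control rule requires a value above 12. An RPE of exactly 12 is therefore moderate in one place and does not meet the threshold in the other.

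**Working it through.** **1. Reproduce the plan's sample size.** Inputs from Sample size calculation: differences of 0.6, 1.3 and 1.6 MMSE points with SDs of 1.2, 2.6 and 3.2; alpha 0.05 (taken as two-sided); power 0.80; attrition 30%.

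- Standardised effect: 0.6/1.2 = 1.3/2.6 = 1.6/3.2 = 0.5 SD in every category group.
- Evaluable per arm: 2 × (1.96 + 0.842)² / 0.5² = 62.8, so 63.
- Randomised per arm: 63 / 0.70 = 90.

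The stated 90 per arm reproduces. The exclusion rule does not enter this calculation and does not make it wrong.

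**2. Bias from removing controls.** Let f be the fraction of controls excluded, and D the amount in SD by which their mean 48-month change is better than that of *retained* controls. The mean of all controls equals (retained mean) + f × D, so the retained mean lies f × D below the mean of all controls. The difference, experimental minus control, shifts by f × D in favour of exercise. If D is negative, the shift goes the other way.

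The documents give neither f nor D. The values below are assumptions.

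| f | D (SD) | Bias f × D (SD) | Share of 0.5 SD | MMSE points in A / B / C |
|---|---|---|---|---|
| 10% | 0.25 | 0.025 | 5% | 0.03 / 0.07 / 0.08 |
| 10% | 0.50 | 0.05 | 10% | 0.06 / 0.13 / 0.16 |
| 20% | 0.25 | 0.05 | 10% | 0.06 / 0.13 / 0.16 |
| 20% | 0.50 | 0.10 | 20% | 0.12 / 0.26 / 0.32 |

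The reference for D matters. If the advantage k is measured against *all* controls instead, the bias is f × k / (1 − f). The same ranges then give 0.028–0.125 SD, or 6–25% of the target. This is the same model with a different reference group.

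**3. Power, if exclusions come on top of the 30% attrition.** Evaluable controls fall from 63 to 63 × 0.9 = 56.7 or 63 × 0.8 = 50.4, with 63 in the experimental arm. The normal approximation is Φ(0.5 / √(1/63 + 1/n_c) − 1.96), where n_c is the number of evaluable controls.

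| Controls lost | n_c | Power, normal | Power, t-test |
|---|---|---|---|
| 0% | 63 | 0.801 | 0.795 |
| 10% | 56.7 | 0.780 | 0.773 |
| 20% | 50.4 | 0.754 | 0.746 |

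If excluded controls are already counted within the 30%, this loss does not arise.

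**The case against.** The best defence is that being excluded from the group need not mean leaving follow-up or every analysis set. The article names intention-to-treat and complete-case analyses separately, so the sentence may have been meant for a restricted set. An article may also leave the handling of such participants to a fuller document. This stands in part: a reader might infer that an intention-to-treat analysis is impossible, and the text does not go that far. The defence does not remove the problem, though. The rule is stated outright, is not limited to any analysis set, and on its ordinary meaning contradicts the announced principle. It is a conflict in the text and not an omitted detail.

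Four further inferences are tempting and are not supported:

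- *The estimate is biased towards exercise.* It is plausible that controls who take up exercise are healthier and decline more slowly, but no section says so. The direction stays conditional.
- *Experimental non-adherers are kept in.* The article states no exclusion for them. It does not state that none is applied.
- *Control numbers will fall below plan.* The 30% is based on drop-outs in similar studies and the length of this one. The article does not say whether excluded controls count within it.
- *The sample size is wrong.* It reproduces.

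The RPE mismatch concerns one scale point and does not bear on the intention-to-treat argument.

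**Conclusion.** The point holds as a conflict between the control-arm rule and the stated analysis principle, and it needs to be corrected. Confidence is high on the conflict and on the absence of a stated counterpart in the experimental arm. It is low on the numerical consequence. The 5–20% of the target effect rests entirely on assumed values of f and D and on excluded controls having the better prognosis. The power figures need the further assumption that exclusions add to attrition. None of these figures should be read as an estimate of what has happened in the trial. Whichever way the bias runs, removing randomised controls for behaviour during follow-up forfeits the protection that randomisation gives.

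**What to change.** Replace the sentence in the Control group section with one to this effect: *control participants who increase their activity remain in follow-up at all scheduled visits and are analysed in the arm to which they were randomised.*

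In addition:

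- Record the change of activity as a deviation. Use it only in a supplementary per-protocol analysis that applies a stated rule to both arms.
- Reconcile the RPE cut-points of the two sections for that supplementary definition. The PASE is already collected, but the article does not show that it yields an RPE intensity. Check that it can identify the trigger before relying on it.
- For controls already removed, keep all data collected so far and invite them to the remaining visits where possible.

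The cost is a wording amendment and continued assessment at visits already scheduled. The number randomised does not change. There are two drawbacks. Activity taken up by controls may dilute the estimated effect, which is a proper part of an intention-to-treat estimate. Visits already missed cannot be recovered, and this is a real limit in a trial that began enrolling in May 2011 with completion estimated for May 2019.

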### Adverse effects

Participants are asked about the presence of any adverse effects, such as musculoskeletal pain or discomfort, at each exercise session, and are monitored for symptoms such as angina and shortness of breath during the exercise classes.

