### Baseline and successive assessments

The potential eligible participants are invited at the Center for Research and Training in Medicine of Aging of the University of Molise to an in-person assessment that includes: 1) general conditions and health status, 2) neurocognitive performances, and 3) physical fitness levels. The three assessments are performed individually in 3 non-consecutive days. The baseline assessments were also used to screen the participants to exclude those that meet exclusion criteria, and to categorize them in A, B or C category groups. Successively, the assessment sessions are repeated at 6, 12, 24, 36 and 48 months to evaluate the differences among time-points.

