#### General conditions and health status assessment

The following information are collected: socio-demographic data, that is age, gender, ethnicity, income, instruction level and marital status; behaviors (e.g. smoking, alcohol consumption); medical history and clinical conditions, evaluated with a pre-defined check-list; anthropometric measures, that is weight, height, body mass index, waist circumference; blood pressure (checked with calibrated mercury sphygmomanometers); blood sample analysis (for assessing the cardiovascular risk), that is glucose, urea nitrogen, creatinine, total cholesterol, HDL and LDL cholesterol, triglycerides, transaminases, and complete blood count; and medications used.

The blood samples are collected after 12 h of fasting, between 8 and 10 am, and they are all analyzed in the central laboratory of the Local Public Health Institute.

Finally, in accordance with the recommendations proposed by the American Heart Association [23], participants with intermediate or high cardiovascular risk, following the classification of the ACSM [24], have to perform an ergometric test, in order to evaluate their effective eligibility for the proposed procedures.

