Nevertheless, despite the increasing interest on the exercise effects on brain health, some authors claimed that the protective effects of exercise on dementia or cognitive impairment may be overvalued [56, 57]. Also, previous studies showed overall that physical fitness levels are not strongly correlated with cognitive performance [58]. This discrepancy in author opinions and results suggests that further high-quality studies, and interventional studies including long follow-up periods and high reproducible exercise interventions, are necessary.

The EPD trial will: (a) evaluate the effectiveness of multimodal exercise program of 48 months in improving neurocognitive functions in individuals aged 50 years or older at different risk of AD; (b) identify the category of subjects and the cognitive function that gets the best benefits from such modality of exercise; c) examine the possible mechanisms by which exercise improve cognition.

In conclusion, this study, if successful, may represent an affordable and safe method to demonstrate that exercise represents a protective tool to delay the onset of dementia and the cognitive impairment in older adults at risk, such as subjects with SMC or MCI. Results of this study are expected to have important public health implications and a profound impact on future AD prevalence.

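### Adverse-effect enquiry is described only at exercise sessions, so session-reported events cannot be compared between arms and the Discussion's safety remark has no like-for-like support

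*Protocol article*

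**What the plan says.** The Adverse effects section is a single sentence with two parts. The first is an enquiry: "Participants are asked about the presence of any adverse effects, such as musculoskeletal pain or discomfort, at each exercise session". The second is observation: participants "are monitored for symptoms such as angina and shortness of breath during the exercise classes".

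The classes belong to one arm. The section on the experimental group says: "Participants randomized to the experimental group are asked to participate in one-hour exercise classes, three times a week, for 48 months". The section on the control group says: "Participants assigned to this group will be strongly encouraged to keep their usual life-style, or continue their usual physical activity, generally of low intensity". No trial sessions are described for controls.

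Both arms share the scheduled assessments. Baseline and successive assessments states: "Successively, the assessment sessions are repeated at 6, 12, 24, 36 and 48 months to evaluate the differences among time-points". The health part of these assessments includes "medical history and clinical conditions, evaluated with a pre-defined check-list", together with blood pressure, blood tests and current medication.

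The Outcomes section lists no safety endpoint, and Statistical analysis describes no comparison of harms. The Discussion closes by saying that "this study, if successful, may represent an affordable and safe method to demonstrate that exercise represents a protective tool".

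**The concern.** The stated route for collecting adverse effects depends on the allocated arm. Participants are aged 50 or over, and controls may themselves walk, stretch, tone or do balance work. Musculoskeletal complaints can therefore arise in either arm. If one arm is asked at every class and no matching question is described for the other, reported events in the exercise arm cannot be separated from background.

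The route also thins out inside the exercise arm. A participant who stops coming because of pain or injury is no longer asked at sessions, so the reports most relevant to tolerability may be the ones lost.

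A by-arm reading of such data could mislead either way: background complaints could be blamed on exercise, or harms could be missed among those who left the classes. The plan itself treats exertional risk as relevant. Aerobic intensity rises to a perceived exertion of 16–17, angina is watched for, and people at intermediate or high cardiovascular risk must pass an ergometric test.

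**Working it through.** **Is there a figure to reproduce?** The plan states no safety figure. Its only sample-size figure, 90 per arm, concerns efficacy and does not bear on this point. It does reproduce: the effect/SD ratio is 0.6/1.2 = 1.3/2.6 = 1.6/3.2 = 0.5, which needs 63 completers per arm (two-sided 5% assumed, 80% power), and 63/(1 − 0.30) = 90.

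**Sources of harm information, side by side**

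| Source | Experimental, attending | Experimental, stopped attending but still in follow-up | Control |
|---|---|---|---|
| Adverse-effect question at sessions | yes | no | none described |
| Symptom monitoring in classes | yes | no | none described |
| Illness check-list at follow-up visits | 5 visits | 5 visits | 5 visits |

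The first two rows follow from the Adverse effects, EG and CG sections. The third follows from the assessment sections, which make no distinction by arm.

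**Opportunities to report**

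- Session enquiries per experimental participant, upper bound: 3 per week × 52 weeks × 4 years = 624. This assumes full attendance and no breaks.
- At the adherence boundary of 50% absence: 0.5 × 624 = 312. A participant classed as non-adherent has fewer.
- Session enquiries per control: none described. The check-list visits number 5 in each arm.
- Controls affected: at least 90 in each of three category groups, 3 × 90 = 270.

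**Why the counts do not measure bias.** Let p be the true event risk in an arm and s the probability that an event is captured. The expected ratio of reported events is (p_E × s_E)/(p_C × s_C). With equal true risks this reduces to s_E/s_C, so any departure from 1 would come from ascertainment alone. The document gives neither s nor any event rate. The ratio of true risks therefore cannot be recovered from session reports, and the size of the distortion cannot be computed.

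**What the check-list can carry.** It is taken at the same visits in both arms, so it could support a limited comparison of newly recorded diagnoses. Its items are not shown. Nothing says that it covers pain, falls, exertional symptoms or hospital admission, or that it serves as adverse-event capture.

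**The case against.** The case on the other side has several parts.

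- A reader might infer that controls are asked nothing about their health. The document does not support this. All participants are due five structured health assessments after baseline, and setting 624 against 0 would ignore them.
- A reader might also infer that follow-up ends for those who leave the classes. It does not say so. More than 50% absence only labels a participant non-adherent, and an intention-to-treat analysis is planned. What is lost is the session-level enquiry.
- A reader might infer that a safety conclusion is planned. None is. The Discussion sentence is conditional, its grammatical subject is the study, and no safety objective, endpoint or analysis appears. Asking at sessions is a sensible way to look after people during supervised exercise.
- A condensed article may leave adverse-event forms to the full protocol.

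The first three stand and limit the point to what is claimed here. The fourth stands only in part. The content of the check-list may well be set out elsewhere, but the article does more than stay silent: it states a collection route, and that route exists in one arm only.

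**Conclusion.** The point holds in a limited form. As described, adverse-effect ascertainment depends on arm and, within the exercise arm, on attendance. Session-reported events cannot support a comparison between arms, and the conditional safety remark in the Discussion lacks a like-for-like basis. The shared check-list softens this for new diagnoses but does not remove it.

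This is a secondary matter. The primary outcome, the sample size and every stated efficacy analysis are unaffected. The size of any bias cannot be given, because the document contains no event rates or capture rates.

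The conclusion rests on two assumptions: that the Adverse effects section describes the whole enquiry, and that the check-list is not already an adverse-event form. If the full protocol shows otherwise, the remaining action is to say so and to name the shared source as the basis for any comparison.

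**What to change.** 1. At the remaining 6-, 12-, 24-, 36- and 48-month assessments, have the blinded assessors put the same neutrally worded questions to all randomised participants in both arms, including those classed as non-adherent. Cover musculoskeletal events, falls and fractures, cardiovascular events and hospital admission. Record deaths for both arms.
2. Base any between-arm safety statement on that source only.
3. Report session-level events separately, as a description of the exercise arm.
4. For visits already completed, disclose the unequal ascertainment and limit the safety wording in the Discussion accordingly.

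**Cost.** A few questions at visits already scheduled, with no added visits or staff. Recall over intervals of 6 to 12 months will be imperfect. Answers could reveal allocation, so the wording must respect the rule in the Blinding section against discussing the exercise programme at follow-up.

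Coverage will also be incomplete. Enrolment began in May 2011, and 48 months of follow-up ending in May 2019 implies last entry around May 2015, so many early visits are probably past and cannot be recovered prospectively. For these, item 4 is the only remedy.
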